#### Executive function assessment

2.5.2.

Targeting executive function specifically, we will perform Trail Making Test (TMT) (53), TMT-Black & White (TMT-B&W) (54) as paper-and-pencil tests, and computerized cognitive function tests (Attention-Switching Task [AST], Stop Signal Task [SST], Spatial Working Memory [SWM]) from the Cambridge Neuropsychological Test Automated Battery (CANTAB) (55). Participants will be seated comfortably in front of a desk and will be asked to perform the tests. The TMT consists of parts A (TMT A) and B (TMT B), in which TMT A is related to visual attention skills and TMT-B is related to executive functions. The TMT-A requires participants to draw lines to connect randomly distributed numbers in ascending order, whereas the TMT-B requires participants to connect numbers and letters alternatively (56, 57). The TMT-B&W is similarly constructed. The TMT-B&W A will prompt the participants to connect the circles containing numbers in ascending order. In contrast, TMT-B&W B will prompt the participants to connect the numbers in consecutive order, alternating between the two color sets (black and white) (54). TMT is measured as the time taken to complete the task in parts A (TMT A) and B (TMT B), and we obtained TMT A, TMT B, TMT-B&W A, and TMT-B&W B from both tests. In addition, we obtained TMT B-TMT A by subtracting TMT A from TMT B, which reflects greater executive function, sequestering psychomotor speed, and visual search (58, 59).

The researcher will administer the CANTAB tests using a two-button press pad connected to a touchscreen tablet computer, following the administration guide. The AST reflects selective attention and cognitive flexibility, along with top-down executive function, measuring cued attentional set-shifting, which manages conflicting information and inhibits task-irrelevant information. In each trial, the participants will see instructions presented on the monitor about which stimulus they should respond to, either the placement (right or left on the screen) or the direction (to the right or left) of an arrow. The participants will then be asked to press the right or left button according to the presented arrow. Thus, some trials will present congruent stimuli (placement and direction are identical), whereas others will display incongruent stimuli (the side on which the arrow appeared), thereby assessing the ability to switch attention between the placement and direction of an arrow. There are two different conditions between the two consecutive trials: non-switched trials (previous and present trials are identical) and switched trials (previous and present trials are not identical). AST outcome measures include response time (RT) and the number of correct trials; latency in congruent, incongruent, and all conditions; and percent correct (rate of correct response). A lower RT or a higher number of correct trials indicate better performance. In addition, we will obtain the following variables: congruency cost (ms, RT in incongruent condition – RT in congruent condition) and switch cost (ms, RT in switched trial – Rt in non-switched trial), in which a lower cost indicates better executive function.

SWM reflects spatial working memory or executive function through a search task, which is the ability to retain and manipulate visuospatial information. In each trial, the participants will be presented with randomly located colored boxes on the computer screen and will be asked to search through those boxes by touching each box to reveal its contents and find all the hidden tokens, in which the number of hidden tokens corresponded to the number of boxes. When they find a yellow token inside the box, it will be moved to, and fill the column on, the right side of the screen. The yellow token is never hidden in the same box twice; thus, the participants will be told to try to find the next hidden token, open the unselected box, and not revisit the previously opened box until they find the token. It is considered an error if the participant opens any box that is already opened. When the participants find a token in each box, the trial ends. As the participants complete each trial, the number of boxes increases from four to six to eight boxes. To reduce errors, the participants must remember where the tokens were previously hidden. The outcomes of SWM are “between errors” and “strategy.” Between errors is defined as the number of revisits to the box in which the participants already found a yellow token in the previous search, with a lower value indicating higher performance. The strategy is the effectiveness of the participants’ searching, in which participants follow a pre-specified sequence beginning with a specific box and return to the same box to start a new sequence. It ranges from 8 to 56, with a higher score indicating noncompliance with a specific strategy and a poor strategy.

The SST measures an individual’s ability to inhibit a response that has already been initiated, in two stages (go and stop trials). (1) Go trial: The subjects are requested to make a speeded response by pressing a button depending on the direction of an arrow pointing (left button for a left-pointing arrow and right button for a right-pointing arrow). (2) Stop trial: If an audio tone (a beep signal) is presented, participants should withhold any response to the stimulus and not press the button. The SST outcome measures include stopped signal reaction time (SSRT) and the proportion of successful stops, which are calculated from the last half of the trials. The SSRT is an indirect estimate of the inhibitory response speed, indicating the time required to abort a pre-potent action in the presence of a stop signal (stop signal delay), which is calculated by subtracting the RT on the stop trial from the mean RT on the go trial. A lower SSRT indicates a faster response and better performance. The proportion of successful stops is obtained with the number of times of successful stops, in which the participant stopped successfully, divided by the total number of stop signals, with higher indicating better performance.

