**Figure 1 fig1:**
[figure not shown]
Examples of rhythm pattern across difficulty level.

VR-MAT-Training consists of four levels of visually guided drumming tasks designed to restore various attention types in a hierarchical manner: (1) MAT-Level 1: One hand drumming, (2) MAT-Level 2: Two hand drumming, (3) MAT-Level 3: Reversed drumming, and (4) MAT-Level 4: Alternating drumming. In VR-MAT Training Level 1, a four-beat rhythm pattern is visually presented on the computer screen, first on the left side, and then independently on the right side. In VR-MAT Training Level 2, the visual cues used in Session Level 1 are combined and presented concurrently. VR-MAT-Training Level 3 is a two-hand drumming task that employs reversed rhythm patterns compared with those used in Level 2. For example, the visual patterns presented on the right side are presented on the left side and vice versa. Because individuals already possess habituated body patterns, they must inhibit previously learned patterns while learning new reverse patterns. Finally, VR MAT Training Level 4 provides the rhythm patterns of Levels 2 and 3 in a randomly alternating manner. Each task includes 20–21 trials, and the completion time is approximately 40 min.

Given the nature of bilateral drumming, the VR-MAT utilizes a familiar four-beat rhythmic pattern with a binary meter. Rhythmic patterns are carefully designed to vary the level of difficulty based on the VR-MAT-Evaluation results. Background music (BGM), originally composed of a binary meter, is selected from the patient’s preferred song list. The BGM can be played by a therapist or recorded without a vocal track. In both cases, adjustment of the BGM tempo is necessary to maintain the baseline tempo of the patients. With the auditory feedback (either a kicking or snaring drum sound), three types of visual cues are given: (a) if the drum stroke is falling within a time range of ±150 millisecond, a flashlight is given (i.e., matched), (b) if the drum stroke is hit earlier than the exact target point, ranging between −300 to −150 millisecond, the ball is exploded (i.e., mismatched), (c) if the ball is missed in the time range mentioned above, no visual cue is presented (i.e., unmatched). Figure 2 shows the user interface of VR-MAT, and Figure 3 presents example rhythm patterns for each of the four training levels.

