#### VR-MAT behavioral data

2.3.1.

We will evaluate the VR-MAT performance four times [pre (day 1), mid1 (day 8), mid2 (day 15), and post (day 22) sessions]. We will obtain (1) the VR-MAT performance accuracy, which is defined as the number of matched strokes divided by the total number of strokes, and (2) the VR-MAT response time (RT), which is the time required for the matched strokes. No background music will be played during the evaluation sessions.

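### The SSRT formula subtracts a stop-trial response time that a correct stop does not have, so as written it does not measure inhibition speed; the VR-MAT accuracy denominator also needs defining

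*Protocol article*

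**What the plan says.** **SSRT (protocol article, section 2.5.2, Executive function assessment).** The stop-signal task has go trials, answered by a button press, and stop trials, on which a tone sounds and "participants should withhold any response to the stimulus and not press the button". The formula for SSRT is given as a difference, "which is calculated by subtracting the RT on the stop trial from the mean RT on the go trial". Just before it, in the same sentence, the article puts the name of the delay in brackets after the stopping time, as if the two were one quantity. The direction of scoring is fixed: "A lower SSRT indicates a faster response and better performance". Both SST outcomes come from the last half of the trials. The second outcome is successful stops divided by all stop signals. On administration, the CANTAB tests are given "using a two-button press pad connected to a touchscreen tablet computer, following the administration guide".

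**VR-MAT accuracy (section 2.3.1, VR-MAT behavioral data).** This is a ratio "which is defined as the number of matched strokes divided by the total number of strokes". The response classes are in section 2.3. A hit is matched "if the drum stroke is falling within a time range of ±150 millisecond, a flashlight is given (i.e., matched"). A hit between 300 and 150 ms early is mismatched. For the third class, unmatched, "if the ball is missed in the time range mentioned above, no visual cue is presented".

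**Use (section 2.7, Statistical analysis).** The neuropsychological outcomes, SSRT among them, are compared between VR-MAT and conventional training. The VR-MAT measures go into a level-by-time ANOVA. Executive function tests and VR-MAT variables are also correlated with each other.

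**The concern.** The SSRT definition conflicts with the task description in its own paragraph. A trial that was stopped correctly produces no press and therefore no RT. The only stop trials with an RT are those where stopping failed. Failed stops are the go responses fast enough to beat the stopping process, so mean go RT minus their mean describes the fast tail of the go distribution, not how long stopping takes. The stop-signal delay, the interval from go stimulus to tone, is what should be subtracted. The sentence names it, but as a label for the stopping time itself, and it never enters the calculation.

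SSRT is one of the executive function outcomes used to compare the two interventions. Scored as written, a real gain in inhibition speed could leave it unchanged or move it the wrong way against the stated rule that lower is better.

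The accuracy question is separate and smaller. If the denominator counts only hits that were made, a participant who lets targets pass without striking is not marked down. Omissions are a failure that an attention measure should register.

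**Working it through.** **1. SSRT: what the formula can use**

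- Correct stop: no press, no RT.
- Failed stop: a press, hence an RT.
- So the written formula equals mean go RT minus mean RT on failed stops.

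**2. SSRT: what that quantity returns**

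The documents give no go RT, delay, SSRT or tracking rule, so the following inputs are assumptions: go RT normal with mean 550 ms and SD 120 ms; true SSRT of 200 to 350 ms. In the race model a stop fails when go RT is below c = delay + SSRT. Let z = (c − 550)/120. Then

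mean go RT − mean failed-stop RT = 120 × φ(z)/Φ(z).

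*Case A: delay set so that half of the stops succeed.* Then c = 550 and z = 0 for every SSRT:

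120 × 0.3989/0.5 = 95.7 ms.

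A simulation of 400,000 trials per setting gave 95.9, 95.8 and 95.3 ms at true SSRT of 200, 250 and 350 ms.

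*Case B: delay fixed at 300 ms.*

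| True SSRT (ms) | c (ms) | z | Written formula (ms) |
|---|---|---|---|
| 200 | 500 | −0.417 | 120 × 0.366/0.338 ≈ 130 |
| 250 | 550 | 0 | ≈ 96 |
| 350 | 650 | 0.833 | 120 × 0.282/0.798 ≈ 42 |

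Here slower stopping gives a lower score, which the article's rule would read as better.

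**3. SSRT: sensitivity to the assumed go RT, and the replacement formula**

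These results come from a simulation with a 50 ms tracking staircase and 200,000 trials per setting. Go RT was normal (mean 500 ms, SD 100 ms), with or without an added exponential tail of mean 100 ms. Half of the stops succeeded in every setting.

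| True SSRT (ms) | Written formula, normal / skewed (ms) | Mean go RT − mean delay, normal / skewed (ms) |
|---|---|---|
| 200 | 67 / 96 | 200 / 210 |
| 250 | 67 / 97 | 250 / 260 |
| 300 | 66 / 96 | 299 / 310 |
| 350 | 67 / 96 | 350 / 360 |

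The written formula is flat. Go RT minus delay recovers the true value to within about 10 ms.

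The replacement has its own condition. In Case B it would give 550 − 300 = 250 ms whatever the true SSRT, so it is valid only where the delay is tracked to about 50% successful stops.

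**4. VR-MAT accuracy: two readings of the denominator**

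Counts are assumed, with 20 targets. Missed means no strike at all.

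| Matched | Early | Missed | Over strokes made | Over cued targets |
|---|---|---|---|---|
| 18 | 0 | 2 | 18/18 = 100% | 18/20 = 90% |
| 10 | 0 | 10 | 10/10 = 100% | 10/20 = 50% |
| 5 | 0 | 15 | 5/5 = 100% | 5/20 = 25% |
| 10 | 5 | 5 | 10/15 = 67% | 10/20 = 50% |

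Section 2.3 calls the participant's hit a drum stroke and the target a ball, which makes strokes made the more literal reading. Section 2.3.1 does not say so expressly.

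**The case against.** **The software may produce the score.** The SST belongs to a published battery run by its administration guide, and the delay appears in the very sentence at issue. That suggests a garbled description, not a chosen analysis. This stands as a limit on the practical impact. It does not remove the error: the guide is cited for administration, and nowhere does the article give a correct scoring formula.

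**The size depends on the delay rule.** The constant of about 96 ms needs half of the stops to succeed, and the article states no such rule. This stands too. A reader might infer that the inhibition outcome simply would not respond to change. The documents do not support so flat a statement: with a fixed delay the score does move, but in the wrong direction. Neither case rescues the formula.

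**Inhibition is not left unmeasured.** The proportion of successful stops is correctly defined, and the attention-switching task also yields a congruency cost. The article names no primary outcome, so SSRT is one of many.

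**The accuracy reading is not certain.** A reader might infer that the plan does divide by strokes made and that an unmatched ball never involves a stroke. Neither is stated. The unmatched class is described by the absence of a visual cue; it could include hits outside the window, and all three classes could be meant to form the denominator. What stands is that the denominator is not pinned down and that its literal reading ignores omissions.

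**Response time on matched strokes only.** A reader might also infer that VR-MAT response time is wrongly truncated at ±150 ms. That assumes it is a signed deviation from the target, which the article does not say. Restricting response time to correct responses is an ordinary choice, so this is not a finding.

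**Conclusion.** The SSRT definition is wrong as written. It contradicts the task description beside it and can be computed only from failed stops. That it does not measure stopping latency follows from the text and the race model. The sizes rest on assumed go RT distributions and delay rules: about 96 ms at any true SSRT with half of the stops successful (66 to 97 ms across the distributions tried), or a fall from about 130 to 42 ms with a fixed 300 ms delay. The effect on the trial's results may be small if the test system supplies the score, which the article leaves open.

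The accuracy point is secondary and conditional. On the literal reading, targets missed without a strike leave the score unchanged. It bears on the level-by-time ANOVA and the correlations only; the VR-MAT versus conventional training comparison does not use this measure.

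**What to change.** In section 2.5.2, delete the formula based on stop-trial RT and do one of two things:

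- define SSRT as mean go RT minus mean stop-signal delay over the last half of the trials, and state that the delay is tracked to about 50% successful stops; or
- state that the SSRT scored by CANTAB is used.

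In the same sentence, stop using the stop-signal delay as a name for the stopping time. Leave the proportion of successful stops as it is.

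In section 2.3.1, define accuracy as matched strokes divided by cued targets, that is matched + mismatched + unmatched, with each target in exactly one class.

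The cost is a few sentences and, at most, a few lines of scoring code. The system already has to compare hit times with target times to classify responses, so no new data are needed.

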### Functional near-infrared spectroscopy

2.6.

We will also examine the hemodynamic changes using fNIRS. The hemodynamic responses will be obtained at a sampling rate of 0.65 s, and the data will be converted to concentrated changes of hemoglobin using the modified Beer–Lambert law. Subsequently, a zero-phase low-and high-pass filter with a cut-off frequency of 0.01–0.09 Hz will be applied using a matrix laboratory (MATLAB) (60–62). Additionally, we will employ vector-based phase analysis to examine multifaceted aspects of cerebral hemodynamic changes (63–66). Vector-based phase analysis is based on an orthogonal vector coordinate plane defined by four indices: oxygenated hemoglobin, deoxygenated hemoglobin, total hemoglobin concentration, and oxygen level changes in the blood vessels. The four indices will be subjected to the calculation of angle k, which indicates the degree of oxygen exchange (66–68), and a scalar L, which indicates the amount of hemoglobin variation (69), and will be further used to calculate the phase-associated response intensity (PRI).

### Statistical analysis

2.7.

We will perform descriptive statistical analysis of the general demographics of the study participants. We define completers as participants who finish 20 sessions of either intervention (VR-MAT or CT) and undergo measurements at 4 weeks of intervention. The statistical analysis will be conducted on an intention to treat basis and the last observation carried forward method will be used to complete the data. Adherence will be reported as the number of completers among enrolled participants. For neuropsychological assessments, a comparative analysis between two different intervention sequences (VC or CV) will be performed and the carry-over effects will be tested using *t*-tests on the change in each sequence for all crossover endpoints (70, 71). For variables with insignificant carry-over effects, the changes in variables during specific interventions from either sequence will be combined and compared. For patients with significant carry-over effects, we will compare the changes in specific interventions during the first period (20 sessions of either intervention). Comparisons between interventions will be performed using a two-tailed *t*-test or the Mann–Whitney *U* test, depending on normality. For music behavior responses obtained from the VR-MAT data, we will perform a two-way repeated-measures analysis of variance (ANOVA) on level (levels 1, 2, 3, and 4) and time (pre, day 8, day 15, and post) with Bonferroni *post-hoc* comparisons.

Repeated measures of correlation between executive function assessment and VR-MAT variables will be examined to determine the linear relationship between paired repeated data using the R package rmcorr from R.3.6.1 (72). The independent variables will remain the same for the analysis of fNIRS data, and the dependent variables will be the PRIs obtained from all channels. All analyses will be performed using the software package R.3.6.1,^1^ and the level of significance will be set to 0.05.

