## Abstract

Attention training is the primary step in the rehabilitation for patients with acquired brain injury (ABI). While active music performance has been reported to aid neural and functional recovery, its efficacy for patients with ABI remains uncertain due to methodological concerns. The purpose of the study is to develop a virtual reality-based music attention training (VR-MAT), which utilizes a visually guided, bilateral drumming in an immersive environment to train attention and executive functions. We also aims to examine the feasibility and effectiveness of the VR-MAT with a small sample size of participants (3–60 months after ABI, *N* = 20 approximately). Participants will be randomly assigned to either a waitlist control or music group, in which VR-MAT will take place five times weekly over 4 weeks (randomized crossover design). The evaluation of VR-MAT performance will include accuracy and response time in music responses. Neurocognitive outcome measures will be administered to quantify pre-post changes in attention, working memory, and executive functions. Additionally, functional near-infrared spectroscopy will be employed to explore the relationships between musical behavior, neurocognitive function, and neurophysiological responses.

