### Study design

2.1.

The present study will be conducted as an assessor-blinded, randomized, controlled trial with a crossover design at a rehabilitation hospital. Participants will be randomly allocated to either the treatment sequence: VR-MAT first and second with conventional cognitive training (CT) (VC group), or in the opposite order (CV group) with an allocation ratio of 1:1 using a computer-generated randomization table. The crossover design is selected because the participants need to serve as their own control group to minimize confounding effects on cognition, which might be markedly affected by a person’s traits, which is not intended by the intervention. In addition, it might be beneficial for the statistical efficiency of this pilot trial, in which VR-MAT had not been attempted for patients with ABI.

Each VR-MAT or CT training period will last 4 weeks with five 30-min intervention sessions per week, resulting in a total of 20 sessions. Therefore, each participant will have received a total of 40 sessions of the intervention, comprising 20 sessions of VR-MAT and 20 sessions of CT. The randomized group assignments were concealed in consecutively numbered sealed opaque envelopes placed in a plastic container. The allocated group will then be determined by the sequential opening of the envelopes after obtaining written informed consent from the participants. Participants will receive a conventional inpatient rehabilitation program (1 h of physical therapy or 30 min of occupational therapy); however, they will not receive a cognitive intervention. Outcome measurements will be performed by a researcher blinded to the group assignment.

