### Outcome measurement

2.5.

Baseline demographic characteristics, including sex, age, diagnosis of ABI, duration after ABI, side of brain lesion, and education, will be collected. Additionally, neuropsychological outcomes will be measured for each participant at baseline, after 20 sessions (4 weeks), and after 40 sessions of intervention (after 20 sessions of alternative intervention; 8 weeks) by a blinded neuropsychologist. We will collect data on neuropsychological outcomes in two ways: global cognitive function and executive function, which are specific targets of VR-MAT. All of the cognitive function tests will be administered in Korean. Additionally, we will obtain VR-MAT behavioral data, which is previously explained, and functional infrared spectroscopy (fNIRS) data (Table 1).

**Table 1 tab1:** List of outcome measurements.

Global neuropsychological assessment	Mini-mental status examination (MMSE)
Clinical dementia rating (CDR)
Global deterioration scale (GDS)
Subjective memory complaint questionnaires (SMCQ)
Executive function assessment	Trail making test (TMT)
	TMT-black & white (TMT-B&W)
	Attention-switching Task (AST)
	Stop signal task (SST)
	Spatial working memory (SWM)
VR-MAT behavioral measures	VR-MAT response time
	VR-MAT accuracy
Functional near-infrared spectroscopy	Oxygenated hemoglobin
	Deoxygenated hemoglobin
	Total hemoglobin concentration
	Oxygen level change

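### The one adherence figure defined pools VR-MAT with conventional training and, on the natural reading, stops at week 4, so it does not isolate adherence to VR-MAT

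*Protocol article*

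**What the plan says.** The Abstract gives as an aim to "examine the feasibility and effectiveness of the VR-MAT".

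Section 2.1 (Study design) randomises participants to VR-MAT followed by CT (VC), "or in the opposite order (CV group) with an allocation ratio of 1:1". On the length of a block it says: "Each VR-MAT or CT training period will last 4 weeks with five 30-min intervention sessions per week, resulting in a total of 20 sessions". Over the whole trial, "each participant will have received a total of 40 sessions of the intervention, comprising 20 sessions of VR-MAT and 20 sessions of CT".

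Section 2.5 (Outcome measurement) schedules neuropsychological assessment "at baseline, after 20 sessions (4 weeks), and after 40 sessions of intervention", the last of these at 8 weeks.

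Section 2.7 (Statistical analysis) defines who is a completer: "We define completers as participants who finish 20 sessions of either intervention (VR-MAT or CT) and undergo measurements at 4 weeks of intervention". It then says: "Adherence will be reported as the number of completers among enrolled participants". The article gives no other adherence or completion measure.

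**The concern.** In a pilot of a new intervention, the share of participants who complete that intervention is a central feasibility result. The figure defined here differs from that share in two ways.

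- **It pools the interventions.** Twenty sessions of CT earn completer status as readily as twenty sessions of VR-MAT. A CV participant qualifies on CT alone.
- **It stops at week 4 on the natural reading.** Section 2.5 attaches the 4-week assessment to the first 20 sessions. A CV participant who leaves before or during VR-MAT in weeks 5 to 8 stays in the numerator.

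At stake is a headline adherence percentage that readers would take as evidence that patients can complete VR-MAT, when up to half of the sample contributes information about CT instead. The faster VR-MAT loses participants relative to CT, the more the figure flatters it.

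**Working it through.** **Inputs**

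- 12 participants per arm, 24 in total (Section 2.2). Check: 2 × 12 = 24.
- 1:1 allocation to VC or CV; 20 sessions over 4 weeks in each period (Section 2.1).
- Attrition of 20% (Section 2.2). The article does not say whether this is over the whole trial or per period, so both are shown.

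**Assumptions (mine).** Enrolled and randomised are the same 24 people; a participant who leaves does not return; everyone who finishes a block attends the assessment that follows it.

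**Definitions.** Let a = VC participants finishing VR-MAT in period 1, b = CV participants finishing CT in period 1, c = CV participants finishing VR-MAT in period 2.

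- Adherence as defined in Section 2.7 = (a + b)/24
- VR-MAT completion = (a + c)/24
- Difference = (b − c)/24

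The difference depends only on the CV participants who finish CT but not VR-MAT. Since b is at most 12 and c at least 0, it cannot exceed 12/24, or 50 percentage points.

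**Step 1: completers with no VR-MAT training.** All 12 CV participants can qualify on CT alone: 12/24 = 50% of the sample.

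**Step 2: equal dropout on both interventions.** Let r be the proportion retained in each period. Then a = b = 12r and c = 12r², so:

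- Section 2.7 figure = r
- VR-MAT completion = (r + r²)/2
- Full 40-session completion = r²

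| Assumed attrition | r | Section 2.7 figure | VR-MAT completion | Full completion |
|---|---|---|---|---|
| 20% over the whole trial | √0.8 = 0.894 | 89% | (0.894 + 0.800)/2 = 85% | 80% |
| 20% in each period | 0.80 | 80% | (0.80 + 0.64)/2 = 72% | 64% |

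In participants, the gap between the two measures is 24 × (0.894 − 0.847) = about 1.1 in the first row and 24 × (0.80 − 0.72) = about 1.9 in the second.

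**Step 3: everyone finishes period 1, then CV participants drop out during VR-MAT.** Here a = b = 12 and only c varies.

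| c | Section 2.7 figure | VR-MAT completion |
|---|---|---|
| 12 | 24/24 = 100% | 24/24 = 100% |
| 9 | 24/24 = 100% | 21/24 = 87.5% |
| 6 | 24/24 = 100% | 18/24 = 75% |
| 0 | 24/24 = 100% | 12/24 = 50% |

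The defined figure does not move in any row. The last row is the extreme case.

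**The case against.** **The wording can be read per intervention.** The 4-week measurement could mean the one that follows whichever 4-week block was completed, since each period has its own 4 weeks and its own assessment. On that reading period 2 is not ignored. The sentence does allow this, so the point about week 4 holds on the natural reading and not with certainty. The pooling survives either way: 20 sessions of CT alone still make a completer.

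**The article may simply be condensed.** A fuller protocol or analysis plan may split adherence by intervention, and the absence of detailed attendance tables is no fault in an article. That is fair. The point here is against a rule that the article does state, and it does not depend on missing detail.

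**Nothing in the effectiveness analysis depends on it.** This is correct. Section 2.7 analyses by intention to treat with last observation carried forward, so completer status does not define the analysis set. The definition also matches the minimum data for the first-period comparison that Section 2.7 uses when carry-over is significant.

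**The extreme case is unlikely.** Also correct. Nothing in the article suggests that all CV participants would finish CT and none would finish VR-MAT. With equal dropout the gap is one or two participants.

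**A stronger reading.** A reader might infer that feasibility goes unmeasured, or that the pilot cannot answer its feasibility question. The article does not support that. It never equates feasibility with this one figure. VC participants who finish period 1 have by definition finished VR-MAT. VR-MAT performance is evaluated on days 1, 8, 15 and 22 (Section 2.3.1), and the Discussion says that accuracy and response time are recorded in every session. The information needed should therefore exist; the fault lies in one summary figure.

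**Conclusion.** The point holds as a fault in a stated definition. The adherence figure in Section 2.7 combines VR-MAT with CT and, on the natural reading, ignores dropout in period 2, so it cannot be read as adherence to VR-MAT.

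If dropout is equal on both interventions, the overstatement is about 4 to 5 percentage points with 20% attrition over the trial and 8 points with 20% per period. It grows when participants finish CT but not VR-MAT, up to 50 points in the extreme. These sizes rest on the planned 24 participants, exact 1:1 allocation and the assumed dropout patterns; the article gives no dropout rate by intervention or period.

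The conclusion concerns how adherence is reported. It does not extend to the treatment comparison or to whether the pilot can assess feasibility at all. The definition should be changed, because the figure bears on a stated aim and the repair is nearly free.

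**What to change.** Replace the single completer definition in Section 2.7 with three counts, each among all randomised participants:

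1. **VR-MAT adherence:** participants who finish the 20 VR-MAT sessions, in whichever period these fall.
2. **CT adherence:** participants who finish the 20 CT sessions, counted the same way.
3. **Full crossover completion:** participants who finish both 20-session blocks and attend the week-8 assessment.

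The cost is a change of wording. Applying the current definition already requires session counts, so no new data collection is needed. The only downside is that the reported adherence to VR-MAT may be slightly lower than the pooled figure.
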